#### (2) Discuss alternative treatments where appropriate.

There are other treatments for alcohol dependence. These treatments include other medications (e.g., acamprosate, disulfiram), various psychosocial therapies, and Alcoholics Anonymous. Participants can also seek naltrexone through their own physician rather than through this study. Participants can also choose to seek no treatment. At the baseline screening, if participants express a desire for a different treatment (or do not qualify for the current study) they will be notified of other treatment options and encouraged to discuss these with their primary care physician.

#### (3) Identify circumstances for terminating the study.

The study can be terminated by the subject at any time for any reason. The subject will be discontinued from the study if he/she experiences a serious adverse event to the medication. The investigators may withdraw participants who do not follow the study protocol (e.g., participants who repeatedly fail to show for appointments or in the case of repeated/excessive non-response to cell phone prompts). Participants who voluntarily discontinue medication may be removed by the investigators, but will always be referred to other treatment resources. Given the nature of cellphone data collection in this study, we will include misuse of the phone (as described previously in this application) as a potential condition under which participants may be removed from the study by the investigators. Situations in which the entire study may be terminated early include the following: If the Principal Investigator or other governing official discovers serious concerns about subjects' safety; because study objectives have been obtained; or in the unlikely event that the Principal Investigator becomes unavailable

and no other additional investigators are able to succeed his role.

vii) Describe procedures for protecting against or minimizing likelihood of identified risks. Include any procedures that will be used to maintain confidentiality as applicable.

**Protection Against Risk:** Participants are informed of all procedures beforehand, and they must read informed consent forms and sign consent forms stating that they understand and agree to the procedures before beginning the study. The following protective measures will also be in place:

**a)** Breach of confidentiality is unlikely because all data are identified only by numeric code and are stored in locked filing cabinets in a designated locked PHI storage area. Identifying information will be collected only for the purpose of contacting participants for their follow-up assessments. The list linking the numerical ID code to the participant's identifying information will be maintained separate and secure from the computerized data files in a locked filing cabinet, and this information will be destroyed immediately after the clinical trial is complete. [name] will oversee entry of all research instruments for the naltrexone trial (i.e., measures outside of AGATE and SASSED) into the Talaria Test Builder (TTB). The TTB is Talaria's proprietary platform for web-based data collection.

**b)** Careful and consistent monitoring of potential side effects and/or adverse events throughout the study is in place. Furthermore, all subjects receive three blood tests (baseline, week 4, week 8), primarily to ensure that liver tests are within a normal range.

**c)** We will maintain an updated list of clinical services and local community practitioners for most psychiatric or substance disorder treatment services for participants, and we will provide appropriate referrals as necessary. Treatment providers in this study are qualified to dispense such advice and will do so when appropriate.

**d)** Normal patient handling procedures are followed to eliminate risks.

viii) Describe the expected benefits, including any possible direct benefit (such as alleviating a condition or providing a better understanding of a participant's condition).

The scientific benefits of the planned study are high, given the scientific importance of finding effective methods for maximizing adherence to pharmacological treatments for alcohol dependence. This study is expected to add to the knowledge base of information on adherence to naltrexone for alcohol problems. Also, it is expected that a proportion of participants will reduce their alcohol use during the current study and all participants will receive free access to an FDA-approved treatment for alcohol problems while enrolled in the study.

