Finally, the participant will pick up his/her 4-week prescription for naltrexone at the UNM Psychiatry Department pharmacy. The pill container will be fitted with a MEMS monitoring system by the pharmacist, which will track the date/time of each time the container is opened. This data, which is stored in a microchip in the MEMS cap. The pillcap will not be linked to any personal identifier or URSI. The data will be downloaded when the participant returns for subsequent visits and labeled by URSI at that point. Data (timestamps) on pillcap openings will be linked to URSI in a password-protected spreadsheet kept on a password-protected computer at MRN. At the end of the baseline appointment participants will be encouraged to contact the study coordinator with any questions, concerns, or problems related to study participation. They will also be encouraged to contact [name] directly with any questions about the study medication or side effects.

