Following the baseline visit, the course of the medication trial will be 8 weeks. During this time participants will come back to MRN/UNM CPR for follow-up medical visits (at weeks 4 and 8). This timeframe is consistent with recommended clinical guidelines for monitoring patients on naltrexone (Anton, 2008). At the Week 4 visit, participants will first be interviewed by the research assistant, who will assess potential side effects using a standard side effects checklist. Results of the interview (i.e., any side effects reported) will be placed in the research folder for [name] to review. Participants will also bring medication bottles for pill counts and uploading of MEMS pillcap data. They will report whether they have had any problems with their study phone or AGATE system.. Participants will report whether they have had any problems with their study phone. Any problems will be documented and addressed. Participants will also complete a brief subset of the study questionnaires again (e.g., assessing drinking and medication adherence in the last 4 weeks, see Table 1). Similar to the baseline visit, participants will be seated alone in a private assessment room at MRN and will complete measures using the web-based interface. Next, a follow-up blood sample will be obtained in the Psychiatry pharmacy using the same procedures and tests as described in the screening visit. Then the participant will meet with [name] for a follow-up medical assessment. [name] will review the contents of the participant's research study folder (e.g., side effect checklist) and interview the participant. If any medical contraindications to continuing naltrexone are evidenced, naltrexone treatment will be discontinued immediately. In these cases, [name] will discuss with the participant an appropriate referral plan. To avoid threats to internal validity, [name] will be blind to study condition (AGATE/SASED). For this reason, she will not discuss aspects of AGATE or barriers to adherence with participants; the interview will be focused on side effects and medical/safety issues. If no contraindications to continuing naltrexone are evidenced, participants will be provided with the next 4-week naltrexone prescription, which will be sent to the pharmacy. Again, pill vials will

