be re-fitted with a MEMS monitoring system pillcap. Participants will not be allowed to take home their prescription on this day, pending results of the blood screen. When the results of the Week 4 blood screen are available, they will be placed in the study chart for review by [name]. If no problems with the bloodwork are evidenced, the research assistant will contact the participant and ask that they pick up their prescription from the pharmacy. If any concerns are noted that suggest medication should be discontinued, [name] will call the participant to inform them.

At week 8 the study physician will complete a visit identical to week 4 (i.e., it will include the same questionnaires, pill counts, blood draw, and medical visit). However, participants will be discharged at the end of the week 8 visit. At the medical assessment, [name] will provide a discharge recommendation. Participants who show evidence of a good clinical outcome to naltrexone will be referred to their PCP. At the end of the 8 week visit the study coordinator will also conduct an exit interview to elicit qualitative information on the usability and acceptability of AGATE/SASED.

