AGATE was designed so that the patient and provider agree upon (or the researcher sets) an adherence goal (e.g. a minimum of 90% of scheduled doses to be taken) over a certain period of time (e.g., 14 days). In the first stage, patients (or research participants) receive a reminder/assessment message for every scheduled dose. If at the end of this period the patient has achieved the goal, the patient progresses to Stage 2, in which the reminder/assessment frequency steps down (e.g., once every few days) for another period of time (e.g., 21 days). If at the end of this period the goal is maintained, the patient progresses to Stage 3, in which the reminder/assessment frequency steps down further (e.g., once per week). However, if the goal is *not* maintained in Stage 2 or 3, messaging frequency steps back up, and patients return to the preceding stage. In this context patients will be provided regular feedback on their performance and reminded of their goal. Participants will also complete daily assessments of drinking behavior (e.g., number of standard drinks per day, urge to drink) throughout the study using the AGATE system. Talaria will collect online metrics of number of messages ignored versus answered and latency to respond to messages to gauge the use/uptake of AGATE and SASED. For the current study, SMS reminders to take medication will be tailored based on the participant's level of adherence to that point. At the outset, participants will be reminded daily to take their medication. Upon achieving adherence for a period several days, reminders will be reduced to once every third day. Please see Appendix V for an example of the AGATE messaging parameters (frequency of reminders, etc).

Participants in the control (SASED) condition will not receive any medication reminders. However, all

participants (AGATE and SASSED) will complete daily drinking measures (e.g., number of standard drinks per day, urge to drink) via the smartphone interface; these assessments will be sent each morning and will be identical across treatment condition.

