### **Participants' Use of Study Cellphones.**

Study cell phones will come activated with a 3-month pre-paid plan with Boost Mobile; these accounts will be maintained by Talaria. During this period participants will be assigned a phone number that will be linked to their URSI number in the Talaria database, but not to any identifying information. Cell phone plans will include unlimited minutes, texts and web access (this was the best option to avoid potential overage charges). Participants will also be allowed to keep their phone at the end of the study if they wish. However, to minimize the possibility of perceived coercion this will not be mentioned until after participants have enrolled in the study (i.e., after providing informed consent). Although participants will be allowed to use the phone for personal calls, texts, browsing, etc., they will be informed of certain limitations to cell phone use during the training provided at the baseline visit (see cell phone agreement form). For instance, participants will be instructed they cannot make international calls, cannot use the phone for illegal or unlawful purposes, and cannot attempt to sell, destroy or deface the phone during the course of the study. Over the course of the study, if the researchers deem that a participant is misusing the phone for these or other reasons, this may be grounds for removal from the study (as noted in the consent form). Once the participant completes the 8-week assessment they will be deemed discharged from the study and will no longer receive text messages from the study. They may continue to use the plan until it expires, at which point the phone number and plan will no longer be active. At that point participants can do as they wish with the phone (e.g., seek another service plan, give it away, etc.). If a participant discontinues the study before the 8-week appointment, they may be asked to return the phone at the discretion of the investigators. However, the investigators will not have any recourse for ensuring return of the phone. If the participant does not return the phone after a maximum of three phone call requests, we will not follow up further.

---

ii) Describe methods by which data will be managed - stored and destroyed.

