**Medication:** The most common side effects of naltrexone reported for the FDA-approved dosage used in this study are gastrointestinal discomfort, nausea, vomiting, headache, and fatigue (Anton, 2008) and a full list of side effects is listed in the consent form. Most side effects are mild and self-limiting and usually occur only during initial therapy. Naltrexone is relatively contraindicated in patients who have liver-enzyme levels that are four to five times above the upper limit of the normal range. Thus, blood tests of hepatic enzymes should be obtained about a month after the initiation of treatment. Such tests can be repeated monthly during a 4-month course of treatment (Anton, 2008). Participants will be told not to take any opiate medication while on naltrexone. Female participants will be instructed to practice consistent contraceptive use (or abstinence) and not to attempt to become pregnant. They will also keep a menstrual diary that will be reviewed with the physician. Participants will be monitored closely throughout the study via side effects check-ups and two medical screens after starting medication.

**Risks Pertaining to Loss of Confidentiality and Privacy:** Confidentiality of participants is a priority for research staff and also is presumed and must be maintained unless the investigator obtains the express permission of the subject to do otherwise. Risks from breach of confidentiality include invasion of privacy, as well as social and economic risks. Economic risks include alterations in relationships with others that are to the disadvantage of the subject, and may involve embarrassment, loss of respect of others, labeling with negative consequences, or diminishing the subject's opportunities and status in relation to others. There are some risks related to the use of cell-phones to collect daily data on drinking and medication adherence. Participants might receive texts while in the company of others and be questioned as to the nature of the message. If a participant leaves his/her phone unattended, it is possible that someone else could view an incoming text message. We will take steps to instruct participants to always keep the phone close by and recommend that the participant sets a password on the phone.

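### A serious adverse event to naltrexone takes the participant out of the study, not only off the drug, so the planned safety bloods and drinking outcomes end with it

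*Protocol*

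**What the plan says.** Section VI. vi)(3) sets the rule: "The subject will be discontinued from the study if he/she experiences a serious adverse event to the medication". The same paragraph treats voluntary stopping of medication differently: there, removal is only an option for the investigators.

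Section V. i) (Procedures, week 4 visit) has a separate rule for contraindications: "If any medical contraindications to continuing naltrexone are evidenced, naltrexone treatment will be discontinued immediately". It adds a referral plan. It neither ends study participation nor says that the remaining visits are kept.

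The safety monitoring is described in two places. Under Medication risks in VI. vi)(1): "Participants will be monitored closely throughout the study via side effects check-ups and two medical screens after starting medication". Under Protection Against Risk, item b), in VI. vii): "all subjects receive three blood tests (baseline, week 4, week 8), primarily to ensure that liver tests are within a normal range".

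Three further provisions bear on what is lost at exit:
- For the electronic pill cap (MEMS), section V. i) says: "The data will be downloaded when the participant returns for subsequent visits and labeled by URSI at that point".
- For the smartphone that carries the daily drinking diary, the section on use of study cellphones says: "If a participant discontinues the study before the 8-week appointment, they may be asked to return the phone at the discretion of the investigators".
- The week 8 visit repeats the week 4 content: "it will include the same questionnaires, pill counts, blood draw, and medical visit".

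**The concern.** Stopping naltrexone removes the drug risk. Leaving the study as well adds no protection against the drug and takes away the monitoring. The order of the rules is also odd: someone who chooses to stop the tablets may stay, while someone seriously harmed by them must go.

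Two things are at stake. The first is safety: the participants with the worst reactions have the least planned study follow-up, and where the event involves the liver, no study blood test would show whether values recovered. The second is completeness of the randomised data. The drinking outcomes of Hypothesis 3 are defined over the 8 weeks, and for these participants the later part would be missing for a reason tied to drug exposure. An analysis plan can choose how to handle missing values, but it cannot recover blood that was never drawn or diaries that were never sent.

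**Working it through.** **Is this only loose wording for stopping the drug?** The week 4 rule ends naltrexone treatment. The voluntary-stop rule treats stopping medication as one event and removal as a possible second one. The serious-adverse-event rule ends study participation. The protocol therefore separates the two ideas and uses study exit here.

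**Does another section restore follow-up?** The statement that all subjects have three blood tests is a general schedule and does not address people who have been removed. The referral plan after a contraindication is clinical care, not study monitoring. The protocol describes no early-termination visit, no follow-up of the event to resolution and no drinking assessment after exit.

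**What one exit costs.** Inputs: 8 weeks of treatment; visits at weeks 4 and 8 (days 28 and 56); a diary every day.

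- Blood tests and medical screens after the start of drug: 2 of each planned. Exit before week 4 loses 2 of 2; exit between weeks 4 and 8 loses 1 of 2.
- Diary days: 8 × 7 = 56. Loss for an exit on day d = 56 − d.

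| Exit day | Diary days lost | Share of 56 |
|---|---|---|
| 7 | 49 | 88% |
| 14 | 42 | 75% |
| 28 | 28 | 50% |
| 42 | 14 | 25% |

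- Pill-cap data at risk = exit day − day of last download. Exit on day 20: 20 − 0 = 20 days, the whole record so far. Exit on day 42: 42 − 28 = 14 days at most, since the second supply is released only after the week 4 blood results.

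**How many participants.** Section VI. ii) plans 105 randomised and 88 at endpoint: 105 − 88 = 17 losses, and 17/105 = 16.2%. The protocol gives no serious adverse event rate, so the rates below are assumptions. Expected removals = 105 × r; chance of at least one = 1 − (1 − r)^105.

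| Assumed rate r | Expected removals | Chance of at least one |
|---|---|---|
| 0.5% | 0.5 | 41% |
| 1% | 1.05 | 65% |
| 2% | 2.1 | 88% |
| 3% | 3.15 | 96% |

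At 1% to 3%, about 1 to 3 participants would leave under this rule, or 1/17 = 6% to 3/17 = 18% of the losses the plan already expects.

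**The case against.** The strongest reply is that the loss is inferred. The protocol does not say that data collection ends at exit, and the consent form and appendices it refers to were not available here. That is correct. The inference rests on mandatory study exit with nothing provided afterwards, and it should be read as such.

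Second, a liver signal in the week 4 bloods is handled by the separate procedure in section V. i), which holds back the next supply and stops the drug without ordering study exit. This stands, and it narrows the liver argument to events that are themselves serious adverse events to the medication.

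Third, there is clinical cover: a check for a primary care provider, referral, and direct contact with the physician about side effects. This is real protection, but it is neither study monitoring nor outcome data.

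Fourth, return of the phone is discretionary and cannot be enforced, the cap could be read when the bottle comes back, and adherence is also measured by pill count and timeline follow-back. The pill-cap loss is therefore only possible, not certain. Pill counts, however, depend on the same visits, as do the questionnaires on drinking and adherence over the last 4 weeks.

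Finally, few people are affected, and both arms take the same drug at the same dose. This stands in full. It limits the size of the point but gives no reason to keep the rule.

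**Conclusion.** The concern holds. A stated conduct rule ends study participation where stopping the drug would be enough, and no section of the protocol provides follow-up afterwards. For each person affected, the cost is one or both of the blood tests and medical screens planned after the start of drug, plus every diary day after exit. In total, perhaps 1 to 3 of 105 participants are involved at an assumed event rate of 1% to 3%; at 0.5% the rule might never be used.

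This is a weakness in safety follow-up and in completeness of randomised data. It is not a demonstrated bias in the primary adherence comparison. The conclusion assumes that the rule is followed as written and that no exit procedure exists in the documents not seen.

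**What to change.** Replace the sentence in VI. vi)(3) with wording such as: naltrexone is stopped if the participant has a serious adverse event to the medication; unless consent is withdrawn, the participant stays in the study and keeps the scheduled visits (bloods, questionnaires, pill count, MEMS download) and the daily drinking diary through week 8, with AGATE medication reminders switched off.

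Add the same follow-up statement to the week 4 procedures in V. i) for any stop ordered by the physician, and let these participants keep the phone until week 8.

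The cost is about two sentences by amendment. The visits already exist, and a diary without medication prompts already runs in the control arm: "Participants in the control (SASED) condition will not receive any medication reminders". The downside is a few extra visits and diary entries by people no longer on drug. Some may be too ill to attend, and they remain free to withdraw. How doses after an ordered stop count towards adherence would also need stating; that can be left to the analysis plan.

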### III. Hypothesis or Study Goals (questions hoped to be answered by study):

The overall goal of the study is to evaluate the efficacy of a new smartphone-based technology for tracking and enhancing medication adherence. The technology, AGATE (Adaptive Goal-Directed Adherence Tracking and Enhancement), was recently developed by our colleagues at Talaria, Inc. (Seattle, WA) for the purpose of enhancing medication adherence for individuals with alcohol problems. In the current study we will test the efficacy of AGATE for increasing medication adherence in an eight-week pharmacotherapy study of naltrexone. Participants will be randomly assigned to smartphone-based adherence support (AGATE) or a control condition (smartphone alcohol and side effects diary, SASED). A secondary goal is to examine medication effects on patterns of daily drinking using ecological assessments permitted by cell-phone assessments.

The specific hypotheses are as follows:

**Hypothesis 1:** Those assigned to the AGATE condition will be more likely to be classified as adherent to naltrexone (e.g., taking 80% or more of scheduled doses) over the course of the study compared to those assigned to SASED.

**Hypothesis 2:** Those in the AGATE condition will take significantly more scheduled doses compared to those in SASED.

**Hypothesis 3:** Those in the AGATE condition will show better drinking outcomes (defined as higher percentage of days abstinent, lower percentage of heavy drinking days, fewer drinks per drinking day, and longer latency to first heavy drinking day) compared to SASED.

**Hypothesis 4:** Those in the AGATE condition will report higher satisfaction with treatment compared to SASED.

**Hypothesis 5:** Medication adherence will moderate the effect of naltrexone on drinking outcomes, such that the effects of naltrexone on reduced heavy drinking will be increased among those with higher rates of adherence.

**Hypothesis 6:** Adherence outcomes will mediate the effects of condition assignment (AGATE vs. SASED) on drinking outcomes.

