#### Overview of Naltrexone Trial

The purpose of the study is to evaluate whether AGATE effectively measures and enhances medication adherence in the context of a naltrexone trial involving heavy drinkers. Participants will be heavy drinkers recruited from the greater Albuquerque area who are interested in either reducing or stopping their drinking and deemed to be candidates for naltrexone pharmacotherapy by the study physician, [name]. Those enrolled in the study will be prescribed naltrexone (at FDA-approved dose of 50mg once daily) for eight weeks. All participants will receive smartphones during the study. Participants will be randomly assigned to receive either AGATE (adherence support) or SASED, a web-based alcohol and side-effects diary via smartphone. The primary outcome will be percent of scheduled doses that were taken during the eight week trial, as measured by the Medication Event Monitoring System (MEMS, Aardex Group, Union City, CA), pill counts, and the timeline follow-back (TLFB) method. The secondary outcomes will be selected indicators of alcohol use over the 8-week trial.

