6. Female participants of child-bearing age must report use of a birth control method deemed adequate by the study physician, must agree to continue this method over the course of the study, and must agree to contact the study physician if pregnancy is suspected during the study.
- 7.

Note: Because naltrexone is efficacious for reducing heavy drinking in non-dependent individuals (Kranzler et al., 2003), a diagnosis of alcohol dependence is not mandatory for inclusion in the study.

ii) Provide approximate number of subjects (both control and intervention groups).

Our goal is to randomize 105 participants. We anticipate this will leave us with 88 participants at study endpoint after accounting for attrition. Based on our previous experience with medication trials conducted at UNM/MRN, we anticipate conducting phone screenings for approximately 300 participants, of which approximately 140 will qualify to proceed to the in-person screening visit. Our liberal estimate is that 25% of these will be screened out for medical contraindications at the medical assessment before 105 are randomized.

iii) What characteristics (exclusion criteria) would exclude subjects, who are otherwise eligible, from this study? (Answer for each subject group, if different.)

Exclusion criteria will consist of the following:

1. Clinically significant physical illness (based on [name] medical evaluation).
2. Pregnancy or intended pregnancy among female participants.
3. Current (30-day) drug use other than alcohol, nicotine or cannabis (as verified by urine toxicology screen).
4. Any recent (90 day) use of opiate drugs or medications
5. Lifetime opioid dependence as assessed by a structured interview.
6. Currently taking any psychiatric medication other than antidepressants.
7. Lifetime diagnosis of a DSM-IV Axis I psychotic disorder.
8. CIWA score of 8 or higher, indicating clinically significant alcohol withdrawal, at baseline
9. Liver enzyme levels greater than 3x the upper limit of the normal range
10. Currently receiving another pharmacological or behavioral alcohol treatment, with the exception of Alcoholics Anonymous.
11. Currently court-mandated to seek treatment for alcohol problems, or otherwise required to document treatment for alcohol problems.

iv) Please see [HRRC Recruitment Guidelines Section 11.2](#) for more information about acceptable recruitment methods. Describe recruitment (source, initial contact method, etc.)

Described under i) above.

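### Investigators may remove randomised participants who stop the medication or ignore prompts, which can end outcome collection in those doing worst on the adherence outcome

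*Protocol*

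**What the plan says.** **Removal rules.** Protocol section VI, vi)(3), on circumstances for terminating the study, states: "Participants who voluntarily discontinue medication may be removed by the investigators". It also states: "The investigators may withdraw participants who do not follow the study protocol". Its examples are repeated missed appointments and withdrawal "in the case of repeated/excessive non-response to cell phone prompts". Phone misuse is a further ground. No count or threshold is given, and no blinded decision-maker is named. Nothing provides for outcome collection after removal.

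**Outcome.** Section V, Overview of Naltrexone Trial: "The primary outcome will be percent of scheduled doses that were taken during the eight week trial", measured by MEMS, pill counts and timeline follow-back (TLFB). Hypothesis 1 in section III adds a binary version: AGATE participants "will be more likely to be classified as adherent to naltrexone", with 80% of doses as the example cut-off.

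**Data collection.** On the MEMS cap, section V says: "The data will be downloaded when the participant returns for subsequent visits". Pill counts and the repeated adherence questionnaires also take place at the week 4 and week 8 visits.

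**Arms and blinding.** Under Overview of AGATE, AGATE starts with a message for every scheduled dose and steps down once the goal is met. SASED receives no medication reminders. Both arms receive the same daily drinking assessment. Blinding to arm is stated only for the study physician.

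**Numbers.** Section VI, ii) plans to randomise 105 and adds: "We anticipate this will leave us with 88 participants at study endpoint after accounting for attrition".

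**The concern.** In an adherence trial, stopping the medication is a poor result on the primary outcome. A rule that makes it a ground for leaving the study lets exit after randomisation depend on the outcome, at staff discretion. Ignoring prompts and missing visits are likely to go with poor adherence too.

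Two things are at stake. First, the people removed may have no visit-based adherence data for the period after removal, and an analysis plan cannot restore data that were never collected. Second, removal may be unequal. AGATE participants have additional messages that they can leave unanswered, and those deciding on removal are not stated to be blind. If removed participants then drop out of the comparison, it is no longer between the groups as randomised. It could show an effect that is absent or hide one that is present.

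**Working it through.** **1. The plan's own figures.** Section VI, ii): 140 × (1 − 0.25) = 105 randomised, which reproduces. Attrition: 105 − 88 = 17, and 17/105 = 16.2%. This is all attrition; the protocol gives no rate of removal by investigators. Everything below is therefore illustration under stated assumptions.

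**2. No true effect, lowest adherers removed.** Assume that adherence among all randomised follows a Beta distribution with mean 0.80 and SD 0.22 in both arms. These values are assumed; the prior study cited in section IV gives a MEMS mean of 0.873 and SD of 0.170. Then a + b = 0.80 × 0.20/0.22² − 1 = 2.306, so a = 1.845 and b = 0.461, and P(adherence ≥ 0.80) = 0.631. Suppose the lowest fraction f is removed and not analysed.
- The adherent rate becomes 0.631/(1 − f), as long as the cut-point for f lies below 0.80, which it does here.
- The mean becomes 0.80 × [1 − G(q)]/(1 − f), where q is the f-quantile and G is the Beta(a + 1, b) distribution function.

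| f | Mean | Adherent rate |
|---|---|---|
| 0 | 0.800 | 63.1% |
| 8% | 0.846 | 68.6% |
| 12% | 0.864 | 71.7% |
| 16% | 0.879 | 75.1% |
| 20% | 0.894 | 78.9% |
| 24% | 0.906 | 83.0% |

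- AGATE 20%, SASED 12%: false difference of +3.0 points in doses; adherent 79% vs 72%.
- AGATE 24%, SASED 8%: false difference of +6.0 points in doses; adherent 83% vs 69%.
- Equal 16%: difference 0, but both arms read 75% instead of 63%.
- If the splits are swapped, the signs reverse.

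**3. Milder mechanism.** Let half of each loss be lowest adherers and half be unrelated to adherence. Only half of f then shifts the distribution. The 20/12 split gives +1.9 points in doses and +3 points in the adherent rate. The 24/8 split gives +3.8 and +6 points.

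**4. A hidden effect.** Assume 5 of 52 lost in AGATE and 12 of 53 in SASED, a mean of 0.873 in those remaining in both arms, and a mean of 0.20 to 0.40 in those lost. The analysis of those remaining shows zero. The true difference at 0.20 is (47 × 0.873 + 5 × 0.20)/52 − (41 × 0.873 + 12 × 0.20)/53 = 0.808 − 0.721 = 0.088. At 0.40 it is 0.828 − 0.766 = 0.062.

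**5. A real effect shrunk by equal removal.** Assume true adherent rates of 60% and 80%, with half of the non-adherers removed in each arm. The rates become 0.60/(0.60 + 0.20) = 75.0% and 0.80/(0.80 + 0.10) = 88.9%. A 20-point effect reads as 13.9 points.

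**6. Scale.** With 44 per arm (1:1 assumed), SD 0.170, two-sided 5% and 80% power (also assumed), the detectable difference is (1.960 + 0.842) × √(2/44) × 0.170 = 0.102, or 10.2 points. A false difference of 2 to 6 points is about a fifth to three-fifths of that.

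**7. What is known without a visit.** If a 4-week supply is 28 once-daily tablets, someone who never collects the second supply can have taken at most 28/56 = 50% of doses, below the 80% example cut-off.

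**The case against.** The strongest reply is that removal is permissive and the protocol never says that removed participants are left out of the analysis. Analysis sets and the handling of missing doses usually belong in the analysis plan, which is not at hand. That stands: a reader might infer that the trial discards its adherence failures, and the text does not say so. What the protocol does fix is a rule that can end data collection, and an analysis plan cannot undo that.

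Nor is the outcome of every removed person wholly lost. Someone removed after week 4 already has MEMS, pill-count and questionnaire data for the first four weeks, and TLFB is also an outcome source. This also stands. The loss is of later data, or of all visit-based data for those removed before week 4.

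Unequal exposure to the prompt rule is an inference. The daily drinking prompt is identical in both arms, so non-response could be judged on that alone. AGATE reminders also step down. Section VI, v) mentions daily drinking and adherence measures without distinguishing arms, which does not sit easily with the account in Overview of AGATE. Imbalance is therefore plausible, but not established.

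The larger illustrations remove strictly the lowest adherers and assume splits found nowhere in the protocol. The planned 17 losses would also include ordinary dropout. The mixed mechanism in step 3 lowers the bias but does not remove it.

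Finally, with only two visits after baseline, a person who repeatedly fails to attend has already missed the downloads. Dropping missed visits as a ground gains less than dropping the other grounds.

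**Conclusion.** The concern holds in a limited form. The protocol permits discretionary, outcome-related removal after randomisation, while its main adherence data depend on attending later visits. That may end outcome collection in the participants with the lowest adherence.

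It would go too far to say that failures are deleted from the analysis, that a removed person's outcome is always lost, or that the rule favours AGATE. The documents state no exclusion rule, preserve the first four weeks for later removals, and determine neither the direction nor the size of any imbalance between arms.

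With no true effect and the assumed splits, the false difference is roughly 2 to 6 points in percent of doses. The upper end is close to a worst case. Equal removal leaves no false difference when there is no true one, but it inflates the adherent rate in both arms and can shrink a real effect. All these sizes assume that removed participants are not analysed.

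**What to change.** Amend section VI, vi)(3) so that voluntary discontinuation of medication, non-response to prompts, missed visits and phone misuse do not by themselves end follow-up. Phone misuse may end phone service. State that being off medication and being out of follow-up are separate. Decisions on stopping naltrexone are unchanged.

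Invite all randomised participants to the week 4 and week 8 MEMS, pill-count and TLFB collection unless they withdraw consent, and analyse them in their assigned arm.

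Count as not taken the scheduled doses after voluntary discontinuation, and those from a second supply that the participant was cleared to collect but did not. Do not apply this to everyone without a second supply: section V holds that supply until the week 4 blood results are reviewed and provides for medical discontinuation. Doses withheld or stopped on medical grounds need their own prespecified rule.

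The cost is one amended paragraph, a sentence on the analysis set and dose counting, some reminder calls, and somewhat lower reported adherence.
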